### Sample size

Based on our observational data on adult CNO patients with a maximum pain score of ≥6/10 treated with intravenous pamidronate, BPI score for maximal pain is expected to decrease from a mean of 8 with standard deviation (±) of 2 to a mean of 6 ± 2 in the active treatment arm. In rheumatoid arthritis, the placebo effect on pain has been estimated at 16-22 at a 100-mm scale.^44^ However, because evidence-based treatments for CNO are entirely lacking—potentially reducing patient confidence in any given treatment—and many patients present with advanced disease due to diagnostic delays, we anticipate a smaller effect in the placebo arm of this trial, with pain levels decreasing from 8 ± 2 to 7.5 ± 2. We use a power of 80% and an alpha of 0.05. As the primary analysis is done with ANCOVA, adjustment for correlation between baseline and follow-up scores was done (Pearson’s correlation coefficient calculated at 0.479), with a required sample size of 35 patients per arm (total *n* = 70).^45^ In case of screen failure or drop-out before the 6-mo primary endpoint, patients will be replaced to meet the required sample of 70.

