## Abstract

Chronic nonbacterial osteitis (CNO) is a rare auto-inflammatory bone disease affecting children and adults. Adult CNO is characterized by painful bone lesions, primarily of the anterior chest wall. There is no approved therapy for adult CNO. Current off-label treatments include intravenous bisphosphonates, which have been shown to alleviate pain through decreasing bone turnover. However, no adequately powered randomized controlled trials (RCTs) have been conducted. This double-blind, placebo-controlled RCT investigates the efficacy of intravenous pamidronate to decrease bone pain in adult CNO patients. Recruiting at the Dutch national referral center for CNO, adult patients with persistent bone pain despite non-steroidal anti-inflammatory drugs, or optionally other standard-of-care treatments are randomized to receive two courses of intravenous pamidronate (at 0 and 3 mo, 30 mg daily, on 3 consecutive d) or placebo. From 6 mo onwards, all patients receive open-label pamidronate for another two courses. The primary outcome is change in score for maximum pain from 0 to 6 mo. Secondary outcomes include change in quantitative intralesional bone turnover as measured on sodium-fluoride positron emission computed tomography ([^18^F]NaF-PET/CT), inflammation markers, shoulder function, general health, quality of life, fatigue, physical, and work activity. The pamidronate for pain in adult chronic nonbacterial osteitis trial addresses the need for evidence-based treatments in adult CNO. Results will directly impact daily clinical practice, either validating the use of intravenous pamidronate in CNO at the dose used in this trial or prompting the search for alternative regimens or agents. This trial was registered in EudraCT (reference 2020-001068-27) and the Dutch Trial Register (reference NL68020.058.20).

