## Materials and methods

### Trial setting and design

This is a single-center, superiority trial conducted at the Centre for Bone Quality of the Leiden University Medical Center (LUMC), which is the Dutch national expertise and referral center for CNO. The trial starts with a 6-mo double-blind, randomized, placebo-controlled phase with 1:1 allocation of pamidronate or placebo (see Figure 2). Double-blind placebo-control was deemed necessary to prevent reporting bias because the trial’s primary outcome is patient-reported pain, which is susceptible to a placebo-effect. The 6-mo treatment duration is based on observational data from our center, where patients typically receive treatment for 6 mo or 1 yr (2 or 4 infusion cycles, administered in 3-mo intervals aligning with the physiological cycle of bone turnover). In consultation with representatives of the Dutch CNO patient association, it was agreed that 6 mo period of potential placebo treatment was acceptable if followed by the open-label extension. Therefore, the 6-mo randomized phase is followed by a 6-mo open-label phase.

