## Discussion

The PAM-CNO trial marks a significant milestone as a first powered double-blind, randomized, placebo-controlled trial investigating the effectiveness of intravenous pamidronate in 3-mo cycles to reduce pain in adults with CNO. As current treatment for CNO relies on expert opinion and scarce observational data, the trial’s outcomes are expected to have direct clinical impact, either validating the use of pamidronate or prompting the search for other effective treatments.^52^

Designing and conducting an RCT for a rare and poorly characterized disease such as CNO presented multiple challenges. First, the considerable worldwide variation in disease definition and the absence of validated classification criteria made it difficult to establish inclusion criteria. Our current inclusion criteria are derived from a structured multidisciplinary assessment that combines typical clinical, biochemical, imaging, and—if bone biopsy is performed—histopathological characteristics. As a national expertise center for CNO, LUMC handles high patient volumes, providing us with extensive diagnostic experience. We therefore anticipate that our study population will be representative of CNO, but acknowledge the importance of developing classification criteria to improve the external validity of future trials.

Recruitment represents a second challenge in trial conduct. The required sample size of 70 patients was initially expected to be recruited over the course of 18 mo starting in December 2020, but this was not achieved due to the rarity of the disease and external factors (such as the COVID-19 pandemic limiting outpatient contacts). While the possibility of expanding to a multicenter trial was considered, this option was rejected due to the variation in disease definition and diagnostic approach, and the limited availability of laboratory infrastructure and [^18^F]NaF-PET/CT at other centers. The recruitment period was extended, and with 61/70 patients included at current, recruitment is anticipated to be completed in the first half of 2025.

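### The stated 80% power does not follow from the plan's inputs: 35 per arm gives about 94% power for 1.5 points and 80% for about 1.2, a margin that a larger placebo response would use up

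*Protocol article*

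**What the plan says.** All planning figures are in the Sample size section of the protocol article.

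- **Active arm.** Maximal pain is expected to fall from 8 "to a mean of 6 ± 2 in the active treatment arm". The source is given as "Based on our observational data on adult CNO patients with a maximum pain score of ≥6/10" who were treated with intravenous pamidronate. No control group is mentioned.
- **Placebo arm.** For rheumatoid arthritis, "the placebo effect on pain has been estimated at 16-22 at a 100-mm scale", which is 1.6-2.2 points on the 0-10 scale. The plan does not carry this over. It says "we anticipate a smaller effect in the placebo arm of this trial" and assumes a fall from 8 to 7.5 with SD 2. Two reasons are given: patients may have little confidence in any treatment because none is evidence-based, and many have advanced disease after a late diagnosis.
- **Error rates and size.** "We use a power of 80% and an alpha of 0.05". The section reports an adjustment for a baseline to follow-up correlation of 0.479 because the analysis is ANCOVA, and arrives at 35 per arm. Drop-outs before 6 months are replaced; no drop-out rate is stated.

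Trial setting and design justifies blinding by a primary outcome "which is susceptible to a placebo-effect". The Discussion expects the results to have clinical impact, "either validating the use of pamidronate or prompting the search for other effective treatments". The Abstract has a similar sentence that ends in "prompting the search for alternative regimens or agents".

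**The concern.** There are two linked problems. First, the power, the sample size and the inputs do not agree, so a reader cannot tell what difference the trial is able to detect. Second, the answer depends heavily on the placebo arm, where the assumption is weakest.

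The active fall of 2.0 is a before-after change in treated patients who were selected for a high score on the outcome itself. With no control group mentioned, it would include any placebo response and regression to the mean. The expected difference is that total minus whatever the placebo arm does. The plan subtracts 0.5, a value argued without a figure from CNO patients.

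If the placebo arm falls further, the true difference shrinks and the power drops quickly. A non-significant result could then be taken as evidence against pamidronate when the trial had little chance of showing the benefit that remained.

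**Working it through.** **Inputs (Sample size section).** Difference 2.0 - 0.5 = 1.5; SD 2 in both arms; r = 0.479; alpha 0.05; power 80%; 35 per arm. Sidedness is not stated, so two-sided is assumed.

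**Step 1: try to reproduce 35 per arm.**

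- ANCOVA residual SD = 2 × √(1 - 0.479²) = 2 × 0.878 = 1.756.
- n per arm = 2 × [1.756 × (1.960 + 0.842) / 1.5]² = 21.5, so 22. With the noncentral t distribution it is 23.

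Other routes from the same inputs:

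| Method | n per arm |
|---|---|
| ANCOVA, 80% power | 22 (23 by t) |
| No baseline adjustment, 80% | 28 (29 by t) |
| Change score, SD 2 × √(2 × (1 - 0.479)) = 2.04, 80% | 30 |
| ANCOVA, one-sided 0.05, 80% | 17 |
| ANCOVA, 90% power | 29 (30 by t) |
| ANCOVA, 95% power | 36 |

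None gives 35. Two routes do, but each needs something the section does not state. The unadjusted 28 inflated for 20% drop-out is 28 / 0.8 = 35, yet no drop-out rate is given and the section says that the correlation was used. ANCOVA with a follow-up SD of 2.5 gives 35 by the t distribution, yet the stated SD is 2.

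**Step 2: what 35 per arm delivers on the stated inputs.**

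- SE of the adjusted difference = 1.756 × √(2/35) = 0.420.
- Half-width of the 95% CI = 1.996 × 0.420 = 0.84 (t with 67 degrees of freedom).
- Power for 1.5 points (noncentrality 1.5 / 0.420 = 3.57) = 94%.
- Difference detectable with 80% power = 1.19, or about 1.2.

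**Step 3: power by placebo fall.** The active fall is held at 2.0, because as an uncontrolled total it already includes any placebo response.

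| Placebo fall | True difference | Power, 35 per arm |
|---|---|---|
| 0.5 (planned) | 1.5 | 94% |
| 0.8 | 1.2 | 80% |
| 1.0 | 1.0 | 65% |
| 1.3 | 0.7 | 38% |
| 1.6 (low end of the rheumatoid arthritis range) | 0.4 | 16% |

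**Step 4: the placebo assumption against its benchmark.** 0.5 / 2.2 = 23% and 0.5 / 1.6 = 31%, so the assumed fall is a quarter to a third of the cited one. The fall at which power reaches 80%, about 0.8, is half of the lowest cited value. To keep a 1.5-point difference at the cited placebo response, the active arm would have to fall by 1.6 + 1.5 = 3.1 to 2.2 + 1.5 = 3.7 points, against the 2.0 that is expected.

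**The case against.** The best defence is that the plan discloses its placebo assumption and argues for it, and that 35 per arm is more than its own inputs require. Both points stand. The placebo fall is a disputable planning choice and no slip, and the surplus patients give real protection, up to a placebo fall of about 0.8. With 61 of 70 patients already included (Discussion), restating the power also changes nothing in the conduct of the trial.

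Four stronger readings are tempting, and the documents do not support them.

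- *That the 80% power depends on a placebo fall of 0.5.* At 0.5 the power is 94%; it reaches 80% at about 0.8.
- *That the plan's own figures leave a drug effect of 0.4 or less.* The subtraction 2.0 - 1.6 is correct, but the 1.6-2.2 points come from rheumatoid arthritis, and the plan expressly declines to apply them to CNO. They are a benchmark, not the plan's expectation. Nor can it be checked from the article whether the cited effect is a within-arm fall comparable with the 2.0.
- *That the plan fixes a two-way decision rule with no inconclusive outcome.* The sentences in the Abstract and Discussion describe expected clinical impact. They set no threshold and do not mention significance, and the Abstract limits its statement to the dose used here. Rules for reading the primary interval may stand in the full protocol or analysis plan, which are not shown.
- *That a non-significant result should count against the regimen only if the interval excludes 1.5.* The plan never presents 1.5 as a minimal important difference. Simulated at 35 per arm, such a rule would still count a true 1.0-point benefit against the regimen 21% of the time.

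**Conclusion.** The point holds as a misstatement of power together with a weakly supported placebo assumption. On the stated inputs, 35 per arm has about 94% power for 1.5 points and 80% for about 1.2 points; 80% power for 1.5 points needs about 23 per arm. The surplus is used up once the placebo fall exceeds about 0.8. A true 1.0-point benefit would then be missed 35% of the time (100% - 65%), and a 0.4-point benefit 84% of the time (100% - 16%).

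This rests on a two-sided 0.05 test, SD 2 in both arms, r = 0.479, 35 analysed patients per arm and an active fall that stays at 2.0. The SD matters: at 2.5, which is an assumption and not the plan's figure, power would be 80%, 47% and 12% at placebo falls of 0.5, 1.0 and 1.6. The documents do not show that the placebo response will be large. They show that the plan gives no CNO figure to rule it out.

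**What to change.** In the Sample size section:

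1. Replace the single power figure. With 35 per arm, power is about 94% for 1.5 points and 80% for about 1.2 points. State the sidedness of the test. If the 35 came from a drop-out allowance or another SD, state that and recompute.
2. Give the power at larger placebo falls beside it, with the active fall at 2.0: 65% at 1.0, 38% at 1.3 and 16% at 1.6.
3. Add that a non-significant primary result will be read with its 95% CI (expected half-width about 0.84) and will not by itself be taken as evidence against pamidronate. No fixed 1.5-point decision rule is needed.

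The cost is wording only, best settled before unblinding. It needs no extra patients and no change to treatment or the primary model. The drawback is that the stated power looks less favourable at larger placebo responses.

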### Outcomes and statistical analyses

The primary outcome of this trial is score of maximal pain on BPI (numerical rating scale 0-10) measured at the end of the 6-mo randomized phase. We will compare the difference between groups by generalized linear mixed model (GLMM) with analysis of covariance (ANCOVA) to account for baseline scores. The primary analysis will be intention-to-treat (see Table 1 and Figure 2). Secondary outcomes include a range of patient-reported,^32^^-^^40^ biochemical, and radiological outcomes, as well as their intercorrelation, baseline factors associated with treatment response,^41^^,^^42^ and cost-effectiveness^43^ (see Table 1 for measurement instruments, statistical analyses, and timepoints). Sensitivity analyses include a per-protocol and an as-treated analysis of the primary outcome. Missing data on the outcomes not evaluated by GLMM are imputed and handled through maximum likelihood techniques. No interim analyses are conducted.

**Table 1 TB1:** Primary and secondary outcomes of the PAM-CNO trial.

	**Outcome**	**Instrument**	**Timepoint of collection**	**Statistical analysis**	**Timepoint of analysis**
**Primary**	Score for maximal pain at CNO lesion sites	BPI	0, 3, 6, 9 and 12 mo	GLMM with ANCOVA	6 mo
**Secondary**	Score for minimal, average, and activity-related pain at CNO lesion sites	BPI	0, 3, 6, 9 and 12 mo	GLMM with ANCOVA	6 and 12 mo
**PROMs**	Shoulder function	SFA			
		SRQ			
	General health	SF-36			
	Quality of Life	EQ-5D			
	Work activity	Work Activity Score			
	Physical activity	IPAQ			
	Fatigue	MVI-20			
	Patient global	PGIC			
	Burden of a relative	Carer-QoL			
	Pain diary	NRS 0-10 for pain	2 d per wk, for entire 1-yr trial span	GLMM	6 and 12 mo
	Achievement of mild pain, as defined by ≤4/10 for maximal pain on BPI	BPI	0, 3, 6, 9, and 12 mo	Chi-square between groups, reported as odds ratio with 95% confidence interval	3, 6, and 12 mo
	Achievement of ≥50% reduction in maximal pain on BPI	BPI	0, 3, 6, 9, and 12 mo		
	% of patients with reduction in standard dose of NSAIDs/COXIBs	-	3, 6, and 12 mo		
**Biochemical**	ESR, CRP	Standard laboratory evaluation	0, 3, 6, 9, and 12 mo	GLMM with ANCOVA	6 and 12 mo
	Pro- and anti-inflammatory cytokines	ELISA			
	Bone markers	ELISA			
	mRNA expression	MLPA	0, 6, and 12 mo		
	T-lymphocyte counts	FACS			

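### The 35 patients per arm cannot be reproduced from the printed ANCOVA inputs, which need 22 to 23 per arm for 80% power; the mismatch is conservative and its source is not shown

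*Protocol article*

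**What the plan says.** The Sample size section of the protocol article gives all the quantities that a two-arm ANCOVA calculation needs, apart from the sidedness of the test.

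- Pamidronate: maximal pain is expected to fall from 8 (SD 2) "to a mean of 6 ± 2 in the active treatment arm".
- Placebo: a smaller response is expected, "with pain levels decreasing from 8 ± 2 to 7.5 ± 2".
- Error rates: "We use a power of 80% and an alpha of 0.05".
- Baseline adjustment: made because the primary analysis is ANCOVA, with the "correlation coefficient calculated at 0.479".
- Result: "with a required sample size of 35 patients per arm", 70 in total.

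No drop-out inflation is stated; patients lost before 6 months are replaced so that the total stays at 70. Trial setting and design specifies a "randomized, placebo-controlled phase with 1:1 allocation of pamidronate or placebo". Outcomes and statistical analyses names a "generalized linear mixed model (GLMM) with analysis of covariance (ANCOVA) to account for baseline scores" as the primary analysis and says that there are no interim analyses, so neither unequal allocation nor an alpha adjustment enters the calculation.

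**The concern.** Adjusting for a baseline score that correlates with the outcome can only lower the required number. Yet the stated 35 lies above what the same means and SD require with no adjustment at all. The section therefore conflicts with its own description of how the number was obtained.

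What is at stake is how the result will be read. If the printed inputs are right, the trial has clearly more than 80% power for 1.5 points, and 80% power for a smaller effect. If the 80% is right, one of the printed inputs is not the one that was used. A neutral result would be interpreted differently in the two cases, and a reader cannot tell which applies.

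**Working it through.** **Inputs** (Sample size section unless noted)

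- Difference at 6 months: 7.5 − 6 = 1.5
- SD: 2 in both arms
- Correlation between baseline and follow-up: r = 0.479
- Power 80%; alpha 0.05, taken as two-sided (assumption)
- 1:1 allocation (Trial setting and design)
- Baseline-adjusted comparison at 6 months, no interim analysis (Outcomes and statistical analyses)

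**Step 1: no baseline adjustment**

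n per arm = 2 × (1.960 + 0.842)² × (2 / 1.5)² = 27.9, so 28. With the t distribution it is 29.

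**Step 2: ANCOVA**

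1 − r² = 1 − 0.479² = 0.7706. Residual SD = 2 × √0.7706 = 1.756.

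n per arm = 27.9 × 0.7706 = 21.5, so 22. With the noncentral t (df = 2n − 3), power is 0.790 at 22 and 0.808 at 23, so 23.

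**Step 3: attempt to reproduce 35 by other analyses**

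| Reading, 80% power | n per arm (normal / t) |
|---|---|
| ANCOVA, two-sided 0.05 | 22 / 23 |
| Unadjusted, two-sided 0.05 | 28 / 29 |
| Change score, SD = 2 × √(2 × (1 − 0.479)) = 2.04 | 30 / 31 |
| ANCOVA, one-sided 0.05 | 17 / 18 |
| Stated | 35 |

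None comes within 2 patients of 35. A one-sided test widens the gap.

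**Step 4: what 35 per arm delivers on the printed inputs**

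SE = 1.756 × √(2/35) = 0.420. Power for 1.5 points is 94.1% (noncentral t, df 67) or 94.7% (normal). A simulation of 20,000 ANCOVA trials gave 94.0%. The difference detectable with 80% power is 1.19 points (t) or 1.18 (normal), that is, about 1.2.

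**Step 5: changes that would produce 35**

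Each of these would do it, and the article does not indicate any of them:

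- ANCOVA with SD about 2.5 and a difference of 1.5 (35 by t at SD 2.49)
- ANCOVA with a difference of about 1.2 and SD 2 (34 / 35)
- ANCOVA with a difference of 1.3 and SD 2.15 (35 by t)
- ANCOVA at two-sided alpha 0.025 and 90% power (35 / 36)
- Variance multiplied by 1 + r² instead of 1 − r²: 27.9 × 1.2294 = 34.3, so 35
- Unadjusted 28 / 0.80 = 35, a 20% allowance for drop-out with the ANCOVA gain discarded

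Several quite different changes reach the same number, so 35 does not identify which one was made.

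**The case against.** The strongest reply is rounding. The correlation is printed to three decimals, but the pamidronate means and all the SDs are whole numbers. An SD of 2.49 prints as 2. An active-arm mean of 6.2 prints as 6 and gives a difference of 1.3, which with an SD of 2.15 also needs 35 per arm. The authors may therefore have calculated correctly from unrounded data and printed rounded figures. This is possible, though the unrounded values are not shown. It stands to this extent: the text proves only that the printed figures do not yield 35. It does not remove the point, because rounding that moves the requirement from 23 to 35 has to be disclosed for the calculation to be checked.

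A second reply is that the error is harmless: on the printed assumptions the trial is larger than it needs to be, and neither type I error nor bias is affected. That is correct, and it makes this a reporting correction and not a design fault.

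A reader might also go further in three directions that the article does not support.

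- That the true power is 94%, or that recruitment could have stopped at 44 to 46. Both hold only if the printed inputs are the real ones, which cannot be established.
- That drop-out was counted twice, once by inflation and again by replacement. No inflation is stated anywhere; the 28 / 0.80 route is only arithmetic that happens to fit.
- That the trial is underpowered because "the placebo effect on pain has been estimated at 16-22 at a 100-mm scale". The section says that this figure comes from rheumatoid arthritis and gives two reasons for expecting less in CNO. One may disagree with that judgement, but it is openly argued and is not an arithmetical error.

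**Conclusion.** The point holds as a mismatch between stated inputs and stated result. The printed figures require 22 to 23 per arm (44 to 46 in total) against the stated 35 (70 in total), an excess of 12 to 13 per arm. Conditional on the printed inputs, 35 per arm gives about 94% power for 1.5 points and 80% for about 1.2.

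This rests on a two-sided alpha and on treating the primary analysis as a baseline-adjusted comparison at 6 months with SD 2 in both arms. The source that the article cites for its sample size method was not available and was not used. The direction is conservative. Which element is wrong (the number, the power, or a rounded or unstated input) cannot be settled from the article.

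**What to change.** Keep 70 patients and correct the Sample size section in one of two ways:

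1. If 35 came from unrounded or additional inputs, print them (means, SDs and any further factor) to enough decimals that the calculation can be repeated.
2. If the printed inputs are the ones intended, state that 35 per arm gives about 94% power for a 1.5-point difference and 80% power for about 1.2 points, with SD 2 and correlation 0.479.

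In either case, state that alpha is two-sided, if that is what was used. The cost is a few sentences. No extra patients are needed, and neither the design nor the conduct of the trial changes.
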